#### Randomisation

Prior to receiving their test result, probands with an ICC in whom a likely pathogenic or pathogenic variant is identified will be randomly assigned to either the intervention or control group. Block randomisation will be used, with variable blocks ranging from size two to six. Randomisation will be stratified for gender, disease type (cardiomyopathies or primary arrhythmia syndromes) and hospital. To ensure allocation concealment, computer software will be used for randomisation, with an allocation rate of 1:1.^32^ Relatives of probands included in the study will be assigned to the group to which the proband was assigned.

Neither participants nor genetic counsellors will or can be blinded for group assignment. The executing researcher also cannot be blinded because of slight differences between the questionnaires administered in the intervention and control groups. Part of the outcome data will be collected using telephone interviews. To minimise bias, these interviews will be conducted by a research assistant following a structured script.

##### Intervention group

In the intervention group, a tailored approach to informing relatives at risk will be provided. In this approach, probands with a likely pathogenic or pathogenic variant will discuss with the genetic counsellor which relatives are at risk of inheriting the familial variant. They will then be asked which of these relatives they prefer to inform themselves at first using a family letter written by the genetic counsellor, and which relatives they prefer to be directly informed by the genetic counsellor with a similar family letter. This will be discussed during routine post-test counselling. In both cases, after 1 month, the genetic counsellor will send the family letter directly to all relatives at risk for whom the proband has provided consent to contact. The proband will be asked to provide contact details of these relatives.

The family letter is standardised for all three participating centres. For the intervention group, the letter also includes a link to a website specifically designed for this study where relatives can find additional information (www.familieleden.erfelijkehartziekten.nl). The information on this website will be tailored to relative’s situations (ie, specified for disease-type, hospital, parenthood, whether relatives have a desire to have children in the future and which information relatives prefer to receive) by asking them to fill out a short questionnaire on their first visit to the website.

##### Control group

In the control group, the standard care approach will be used. If a likely pathogenic or pathogenic variant is identified, probands assigned to the control group will be asked by the genetic counsellor to inform relatives at risk about the genetic test result, the consequences of this result for relatives and the advice regarding predictive DNA testing and/or cardiac monitoring. This will be discussed during routine post-test counselling. Probands will be supported in informing relatives at risk by a family letter written by the genetic counsellor. This family letter is also standardised for all three participating centres. However, this letter does not include the link to the website with tailored information described earlier, but does include a link to a general website on ICCs (www.erfelijkehartziekten.nl).

#### Measurement time points

For secondary outcome measures, participating probands will be asked to complete a questionnaire 1 month after receiving the genetic test result (T1) and to complete a second questionnaire 9 months after the test result (T2). Before T1 and T2, a short structured telephone interview will be conducted about participant’s knowledge of which relatives are at risk of ICCs and which relatives are informed, because these items are expected to be too complex to answer in a questionnaire.^33^ Participating relatives will complete one questionnaire after attending genetic counselling.

### Measures

#### Primary outcome measures

To assess the effect of a tailored approach to informing relatives at risk, the difference between the intervention and control groups in uptake of (1) genetic counselling and (2) predictive DNA testing of relatives at risk will be measured. To do this, the number of relatives attending genetic counselling and the number of relatives who are genetically tested in the first year after detection of the likely pathogenic or pathogenic variant in the proband will be collected in the laboratories of each participating centre. DNA test results of relatives counselled in non-participating centres will also be taken into account because, in the Netherlands, predictive DNA testing of relatives is always performed in the same laboratory where the proband was tested.

The number of relatives attending genetic counselling and undergoing predictive DNA testing will be compared with the total number of relatives at risk of inheriting the variant who are eligible for genetic counselling and predictive DNA testing based on family pedigrees. For relatives who attend genetic counselling but decide against predictive DNA testing, subsequent attendance of cardiac monitoring will be checked.

Relatives at risk who are eligible for genetic counselling and predictive DNA testing are first-degree relatives and second-degree relatives if there is a connecting deceased first-degree relative suspected of having an ICC. Following the Dutch clinical guidelines for cardiomyopathies, relatives at risk are eligible for genetic counselling and predictive DNA testing from the age of 10 years. For primary arrhythmias, depending on the specific arrhythmic disorder, relatives at risk are eligible for predictive DNA testing from birth.

Furthermore, conditional uptake of relatives at risk, defined as the number of relatives who are genetically tested relative to the number who attend genetic counselling, will be calculated. Uptake will be measured at randomisation condition (intervention or control group) and family level.

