### Sample size calculation

The study aims to detect a difference of 15% in uptake of genetic counselling by relatives between the control (usual care, 50%) and intervention groups (tailored approach, 65%). Assuming a two-sided 5% significance level and a power of 80%, 340 relatives (170 in each group) would be required to participate in this study. On average, six relatives per proband are at 50% risk of inheriting the variant, including children and adults.^9^ With a conservative estimate of four eligible adult relatives per proband at risk, 85 probands with an ICC and an identified likely pathogenic or pathogenic (class 4 or 5) variant will need to be included in this study to reach 340 relatives. A likely pathogenic or pathogenic variant is found in, on average, 20% (lower margin) of all probands with a suspected ICC. With an expected response rate of 70% and a drop-out rate of 20%, approximately 759 probands will be approached to participate in the study.

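### As described, relatives counselled outside the three centres enter the data only through a DNA test, so counselling uptake is understated and conditional uptake overstated

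*Protocol article*

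**What the plan says.** Under Primary outcome measures, the protocol article names two primary outcomes over the first year after the variant is found in the proband: uptake of genetic counselling and uptake of predictive DNA testing. The counts for both "will be collected in the laboratories of each participating centre". For relatives seen elsewhere it adds that "DNA test results of relatives counselled in non-participating centres will also be taken into account", because predictive testing in the Netherlands is always done in the laboratory that tested the proband. The denominator is every eligible at-risk relative in the pedigree, wherever that relative is seen.

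The same section introduces conditional uptake, "defined as the number of relatives who are genetically tested relative to the number who attend genetic counselling". It also recognises that some relatives are counselled and then decline the test, since it plans to check whether they attend cardiac monitoring.

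The Sample size calculation rests on the counselling outcome: "The study aims to detect a difference of 15% in uptake of genetic counselling by relatives", 50% under usual care against 65% under the tailored approach.

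**The concern.** The reason given for capturing relatives from other centres works for testing, because the sample returns to the proband's laboratory. It does not work for counselling attendance, because a relative who is counselled elsewhere and declines sends no sample. On the only route described, that relative is recorded as not counselled but still counts in the denominator.

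Two consequences follow whenever some relatives are seen elsewhere and some of them decline:

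- Counselling uptake, the outcome that sets the sample size, is understated.
- Conditional uptake is overstated. Participating-centre relatives enter it whether tested or not, while outside relatives enter only if tested.

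The article does address relatives from other centres, and its rule fits one primary outcome and not the other. This is therefore a mismatch in what is stated, rather than detail left to a fuller document.

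**Working it through.** **Inputs from the protocol article.** Uptake of 50% versus 65%, two-sided 5%, 80% power and 170 relatives per group (Sample size calculation); 1:1 allocation (Randomisation).

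**Inputs assumed, because the documents give neither.** *s* is the share of counselled relatives who are seen outside the three centres, taken as 10-40%. *d* is the share of counselled relatives who decline testing, taken as 5-20%.

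**Step 1: reproduce the plan's figure.** The article states: "Assuming a two-sided 5% significance level and a power of 80%, 340 relatives (170 in each group) would be required". With the pooled-variance formula and no continuity correction,

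n = [1.960·√(2·0.575·0.425) + 0.842·√(0.50·0.50 + 0.65·0.35)]² / 0.15² ≈ 169.3,

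which rounds up to 170 per group and 340 in total. Power at 170 per group is 80.2%. The plan's figure reproduces.

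**Step 2: look for another source of attendance data.** The telephone interviews (Measurement time points; Participants' characteristics) cover who is at risk, who has been informed and whether the proband intends to inform others. They are not described as covering attendance. Relatives are recruited only in participating centres (Recruitment and consent). Neither source is described as filling the gap.

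**Step 3: express what would be recorded.** Let *p* be the true counselling uptake, and count outside relatives who are tested as counselled.

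- Recorded counselling uptake = p(1 − s·d)
- Recorded conditional uptake = (1 − d)/(1 − s·d), against a true value of 1 − d

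**Step 4: equal shares in both arms.** Power is at 170 per group by the method of Step 1.

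| s | d | Recorded uptake | Difference (points) | Power | Conditional uptake: true → recorded |
|---|---|---|---|---|---|
| 0 | any | 50.0% v 65.0% | 15.0 | 80.2% | unchanged |
| 10% | 5% | 49.8% v 64.7% | 14.9 | 79.7% | 95% → 95.5% |
| 10% | 10% | 49.5% v 64.4% | 14.9 | 79.2% | 90% → 90.9% |
| 20% | 10% | 49.0% v 63.7% | 14.7 | 78.3% | 90% → 91.8% |
| 40% | 10% | 48.0% v 62.4% | 14.4 | 76.3% | 90% → 93.8% |
| 40% | 20% | 46.0% v 59.8% | 13.8 | 72.4% | 80% → 87.0% |

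For s = 20% and d = 10%: 1 − 0.20·0.10 = 0.98; 50% × 0.98 = 49.0%; 65% × 0.98 = 63.7%; 0.90/0.98 = 91.8%.

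**Step 5: unequal shares, d = 10%.**

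- s = 10% control, 30% intervention: 50(1 − 0.01) = 49.5 and 65(1 − 0.03) = 63.05. The difference is 13.55 points, with power 71.4%.
- s = 30% control, 10% intervention: 50(1 − 0.03) = 48.5 and 65(1 − 0.01) = 64.35. The difference is 15.85 points, with power 84.1%.

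The direction depends entirely on which arm has more relatives seen elsewhere.

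**The case against.** **The article never says that outside relatives count only if tested.** It is a condensed account, and the full protocol may describe how attendance elsewhere is traced. The planned check on cardiac monitoring in relatives who decline testing implies some source besides test results, at least in the participating centres. This stands as a limit: the point concerns the only route the article describes. It does not remove the mismatch, because the article gives a rule for outside relatives and justifies it by a fact about testing alone.

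**The effect may be small.** This also stands. At s = 20% and d = 10% the difference loses 0.3 points and power falls by about 2 percentage points. Equal shares create no false effect.

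**A reader might infer that the bias runs against the intervention,** because letters posted by the counsellor could reach more distant relatives. The documents do not establish this. Letters go only to relatives whom the proband agrees to have contacted and whose details the proband is asked to supply, and nothing is said about distance.

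**A reader might also infer a large distortion.** With d = 15% and shares of 20% in control and 40% in intervention, the recorded uptakes are 48.5% and 61.1%, a difference of 12.6 points. Suppose, however, that the first 50 points of intervention uptake keep the control share, so that 10 of them are seen elsewhere. A 40% overall share needs 0.40 × 65 = 26 points elsewhere, so 16 would have to come from the 15 added points, which is impossible. If the added relatives are instead twice as likely to be seen elsewhere (40%), the intervention share is (10 + 6)/65 = 24.6%. The recorded difference is then 62.6 − 48.5 = 14.1 points, and a true conditional uptake of 85% reads 88.3% against 87.6%, a gap of less than 1 point.

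**Conditional uptake has no stated inferential role.** It is to be calculated, and the Statistical analysis section assigns it no comparison between arms. It would be too strong to treat it as the trial's test of whether relatives are pressed into testing. It is still a planned result, and as described it is biased upward.

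**Conclusion.** The point holds in a limited form. On the text as written, a relative counselled elsewhere who declines testing is lost from the counselling count but kept in the denominator. The direction follows for any s and d above zero: counselling uptake is too low and conditional uptake too high. Testing uptake is unaffected, provided that testing always takes place in the proband's laboratory, as the article states.

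The size cannot be derived from the documents. Over the assumed ranges with equal shares, the loss is 0.1 to 1.2 points of the 15-point difference and 0.5 to 7.8 percentage points of power. A conditional uptake of 90% is overstated by 0.9 to 3.8 points. A bias in the comparison itself, in either direction, requires the outside share or the decline rate to differ between arms, and the documents give no evidence on that.

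One ambiguity remains. The article does not say whether outside relatives who are tested enter the counselling count; the figures above assume that they do. If they entered only the testing count, s = 20% and d = 10% would give a conditional uptake of 0.90/0.80 = 112.5%. That impossible value argues against the reading, but the rule should be stated.

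**What to change.** Four changes, none of which needs new data:

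1. Compute conditional uptake, numerator and denominator alike, only among relatives counselled in the participating centres.
2. Report by arm the share of counted relatives who were counselled elsewhere, and state that those who were tested count as counselled.
3. State that counselling uptake is a lower bound as regards relatives seen elsewhere.
4. Read the counselling result alongside testing uptake, which is fully captured and already a primary outcome.

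The cost is a smaller denominator for conditional uptake, which then describes participating-centre relatives only.

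Attendance data from other centres, obtained identically in both arms, would close the gap but should be optional. These relatives have not enrolled, and the Ethics and dissemination section requires informed consent from each participant, so it can be done only where consent allows. Asking probands at the T2 interview is a weaker substitute. They are unblinded, their knowledge may differ by arm because the counsellor informs some relatives in the intervention group, and an interview at 9 months misses the last 3 months of the uptake year.

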### Participants’ characteristics

To assess whether randomisation succeeded and whether characteristics of participating probands and relatives have influenced the primary and secondary outcome measures, sociodemographic and clinical factors will be collected, including gender, education level, ethnicity, living situation and parenthood, family history and the diagnosis of the probands at T1. Relatives will additionally be asked what their degree of kinship is with the proband.

For the same reason, psychosocial and personality factors will be assessed in both probands (at T1) and relatives. Coping style will be assessed by using the shortened version of the Threatening Medical Situations Inventory (TMSI).^37 38^ The TMSI assesses a ‘monitoring’ versus ‘blunting’ coping style related to a medical threat, and it was previously evaluated in an oncogenetic patient population.^37 39^ The shortened version of the TMSI contains two subscales, both consisting of six items on a 5-point Likert scale (1 = ‘Totally not applicable’ to 5 = ‘Totally applicable’; range 6–30). Reliability and validity are satisfactory.^37 38^ The Trait subscale of the State Trait Anxiety Inventory (STAI) will be administered to assess trait anxiety in both probands and relatives.^40^ The STAI is frequently used in research settings and consists of 20 items on a 4-point Likert scale (1 = ‘Not at all’ to 4 = ‘Very much so’; range 20–80).^40^ The reliability and validity for the Dutch translation of the STAI are assessed as good.^41^

Self-efficacy and perceived motivators and barriers regarding informing relatives at risk will be assessed using an adapted version of the ‘motivation’ and ‘self-efficacy’ subscales of the Informing Relatives Inventory (IRI).^42^ The IRI was developed and evaluated in an oncogenetic patient population, and showed satisfactory reliability and validity.^42^ The ‘motivation’ subscale consists of 30 items on a 5-point Likert scale (1 = ‘No role’ to 5 = ‘A large role’; range 30–150), and the ‘self-efficacy’ subscale consists of 7 items on a 4-point Likert scale (1 = ‘Not sure at all’ to 4 = ‘Very sure’; range 7–21). Probands will also be asked to answer a self-constructed item during the telephone interviews regarding whether relatives were informed and whether probands intended to inform (remaining) at-risk relatives.

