### Data analysis

#### Statistical analysis

Sociodemographic, clinical, psychosocial and personality variables will be analysed using descriptive and frequency statistics. An intention-to-treat approach will be used. SPSS V24.0 will be used to perform statistical analyses.^44^ An α level of p<0.05 will be used. Analysis of variance and χ tests will be used to assess differences (1) in sociodemographic, clinical and psychological characteristics between the intervention and control groups and (2) in participants and non-participants, as appropriate. Descriptive and frequency statistics will be used to describe the primary outcomes: (1) uptake of genetic counselling and (2) uptake of predictive DNA testing. Logistic regression analysis will be conducted to assess differences between the intervention and control groups on the primary outcomes, with the randomisation group as the main exploratory variable. Two logistic regression models will be used, with the first model including only the randomisation group and the second model also including the potential covariates (ie, sociodemographic, clinical and psychological variables). Multilevel analyses will be performed to assess whether the randomisation group, that is, the independent variable, has an impact on family and psychological functioning, that is, the secondary outcome variables. The two measurement time points in probands will be treated as nested within probands. To prevent influence of potential confounding factors, multilevel analysis will be adjusted for covariates as well. Participant appreciation of the approach used will be described using frequency statistics.

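### Relatives' covariates for the adjusted uptake model, kinship included, come from a questionnaire completed only after counselling, so non-attenders have none; the pedigree can supply kinship and age group for every eligible relative

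*Protocol article*

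**What the plan says.** All references are to the Protocol article.

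- **Denominator (Primary outcome measures).** Uptake is set against the total number of at-risk relatives "who are eligible for genetic counselling and predictive DNA testing based on family pedigrees". Eligible relatives are first-degree, or second-degree through a deceased first-degree relative suspected of having the condition. The age limit is 10 years for cardiomyopathies; for primary arrhythmias it can be birth, depending on the disorder.
- **Covariate source (Participants' characteristics).** Sociodemographic, clinical, psychosocial and personality factors are collected to see whether they influenced the primary and secondary outcomes. They describe participating probands and relatives. On kinship: "Relatives will additionally be asked what their degree of kinship is with the proband".
- **Timing (Measurement time points).** Participating relatives complete a single questionnaire, after they have attended counselling. Under Participants, it is offered only to adults who make an appointment and can read and write Dutch.
- **Model (Statistical analysis).** Two logistic models are planned for the primary outcomes. One has randomisation group alone, and the other is described as "the second model also including the potential covariates (ie, sociodemographic, clinical and psychological variables").
- **Design (Randomisation).** Probands are allocated ("computer software will be used for randomisation, with an allocation rate of 1:1"), stratified by gender, disease type and hospital. Relatives follow their proband.

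**The concern.** A covariate in a model for counselling uptake must be known both for relatives who attend and for those who do not. The stated source of relatives' covariates gives values only to attenders. With complete cases, a counselling model using any of them would contain only relatives with the outcome "yes", and nothing could be estimated. A DNA-testing model using them would be confined to counselled respondents. It would then address something close to what the article calls conditional uptake, which is a different quantity from uptake among all eligible relatives.

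Minors are in the denominator but outside the questionnaire's inclusion criteria, so they never have a value.

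Kinship and age group are plausible predictors of uptake, and the mix of relatives can differ between arms by chance when about 85 families are randomised. Covariates known for everyone would recover some precision, but the article names none at the level of the relative.

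**Working it through.** **1. The plan's own figures.** "Assuming a two-sided 5% significance level and a power of 80%, 340 relatives (170 in each group) would be required". With p1 = 0.50, p2 = 0.65 and mean 0.575, using the pooled-variance formula without continuity correction:

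n per arm = [1.96·√(2·0.575·0.425) + 0.8416·√(0.25 + 0.2275)]² / 0.15² = 169.3, rounded up to 170, so 340 in total. Power at 170 per arm is 80.2%.

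Then 340/4 = 85 probands, and 85/(0.20·0.70·0.80) = 758.9, which gives 759. All three figures reproduce and none is disputed.

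**2. Who has which variable.**

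| Variable | Stated source | Attenders | Non-attenders |
|---|---|---|---|
| Proband gender, disease type, hospital | Stratification at randomisation | yes | yes |
| Other proband characteristics | Proband, mainly questionnaire at T1 | if the proband responds | if the proband responds |
| Relative's kinship | Relative's questionnaire | adult respondents only | none |
| Relative's other characteristics | Relative's questionnaire | adult respondents only | none |
| Kinship degree and age threshold | Implied by the eligibility rule | yes | yes |

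The last row is an inference. The rule cannot be applied to a pedigree without these facts, but the article does not say that they are recorded. An adult/minor split also needs slightly more than the threshold itself.

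**3. What pedigree covariates would gain.** The article gives no uptake by relative type, so these inputs are assumed:

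- share π of relatives in a lower-uptake category (second-degree or minor): 20% to 50%;
- uptake gap d between categories: 10 to 30 points;
- within-family correlation ρ of relative type: 0 to 0.3;
- within-family correlation (ICC) of uptake: 0 or 0.1;
- four relatives per family and 170 relatives per arm, as in the sample size section.

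*Variance explained:* R² = π(1−π)d² / (0.575·0.425).
- Smallest: 0.16·0.01/0.2444 = 0.7%.
- Largest: 0.25·0.09/0.2444 = 9.2%.

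*Chance shift in the unadjusted contrast:* SD = d·√[π(1−π)·(2/170)·(1+3ρ)].
- Smallest: 0.10·0.043 = 0.4 points (95% range about ±0.9).
- Largest: 0.30·0.075 = 2.2 points (95% range about ±4.4).
- For comparison, the unclustered standard error of the contrast is √(0.4775/170) = 5.3 points.

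*Power,* approximated by replacing n with n/(1−R²):

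| ICC of uptake | Relatives per arm before adjustment | Power unadjusted | Relatives per arm after adjustment | Power adjusted | Gain, points |
|---|---|---|---|---|---|
| 0 | 170 | 80.2% | 171.1 to 187.2 | 80.4% to 83.8% | 0.2 to 3.6 |
| 0.1 | 170/1.3 = 130.8 | 69.1% | 131.6 to 144.0 | 69.4% to 73.3% | 0.3 to 4.2 |

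**4. Simulation check.** 85 families of four, π = 0.3, ρ = 0.3, family effect with SD 0.6 on the logit scale, linear model with cluster-robust standard errors, 1,000 runs per setting:

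| Gap d | SD of contrast, unadjusted to adjusted | Power, unadjusted to adjusted |
|---|---|---|
| 10 points | 5.85 to 5.83 | 65.9% to 66.2% |
| 20 points | 5.71 to 5.63 | 68.7% to 70.6% |
| 30 points | 6.00 to 5.61 | 66.3% to 70.5% |

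The mean contrast was about 14 points with or without adjustment. With no treatment effect, the rejection rate lay between 4.5% and 6.1%.

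**The case against.** The strongest objection is that the choice of covariates belongs in an analysis plan, which is not shown. The article's covariate classes are broad and its list of characteristics is open, so pedigree kinship and age could be added without contradicting anything. This stands as far as a missing covariate name goes. It does not answer the narrower point: the article does state a source for relatives' kinship and other characteristics, and that source cannot serve the counselling model.

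Three stronger readings are tempting, and the documents support none of them.

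- *All covariates for uptake depend on questionnaires.* Proband gender, disease type and hospital are known for every family at randomisation. Proband-level covariates apply to attenders and non-attenders alike, so an adjusted model can still be fitted with them.
- *Family make-up biases the uptake contrast.* Allocation is random, so a chance imbalance is part of the standard error once family clustering is handled. The simulated mean did not move.
- *Nothing in the design balances family make-up.* The age from which minors are eligible depends on disease type, which is a stratification factor, so part of the adult/minor mix is balanced.

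Two technical reservations also stand. The R² arithmetic belongs to a linear model of the risk difference. In the planned logistic model, adjustment changes the odds ratio being estimated and does not shrink its standard error in the same way. Also, the sample size counts adult relatives, whereas the outcome denominator includes minors, so 170 per arm is only a working figure here.

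**Conclusion.** The point holds, at low priority. As stated, relatives' own covariates are missing for every non-attender and cannot enter the second logistic model for counselling uptake. Kinship degree and age group could be taken from the pedigree for the whole denominator, on the reasonable inference that applying the eligibility rule records them. The group-only model remains valid in this respect.

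The benefit is precision. It is about 0.2 to 4 points of power and R² of about 1% to 9%, if uptake differs by 10 to 30 points between types of relative. It is hardly visible at the lower end of that range. These figures rest wholly on assumed shares, gaps and correlations.

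**What to change.** In the adjusted model for both primary outcomes, use for every eligible relative:

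- kinship degree from the pedigree, as at randomisation (or, more finely, child, sibling, parent, second-degree);
- age group (minor or adult) from the pedigree, as at randomisation;
- the stratification factors: proband gender, disease type and hospital.

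Handle family clustering in this model. State that relatives' questionnaire variables, self-reported kinship included, are not used in it; they can still serve the secondary outcomes.

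The cost is two columns in a denominator list that has to be drawn up anyway, and a sentence of analysis wording. With three hospitals, the extra parameters number 1 + 1 + (1 + 1 + 2) = 6 with kinship as first or second degree, or 3 + 1 + 4 = 8 with the finer grouping. The adjusted odds ratio is then conditional on these covariates and should be reported as such beside the unadjusted result.
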